#### ***Mental health measures***

The ‘Kessler 6’ scale (K6) [57] will be used to assess psychological distress in the past month. Two questions from the ‘Kessler 6 plus’ (K6+) scale will also be included to assess the impact of distress on students’ lives. Depression symptoms will be measured using the ‘Patient Health Questionnaire 8’ (PHQ8) [58], while anxiety symptoms will be measured by the ‘Generalised Anxiety Disorder *7*-item scale’ (GAD-7) [59]. The 3-item ‘Mini Social Phobia Inventory’ will screen for social phobia [60]. Quality of life will be measured by the ‘Child Health Utility 9D’ (CHU 9D) [61,62]. The 25-item ‘Strengths and Difficulties Questionnaire’ (SDQ) [63] will be used to assess both positive and negative attributes of the students. Participants’ knowledge about coping with anxiety and depression will be assessed by twelve questions that cover appraisal, reality focused coping and emotion focused coping.

#### ***Personality type***

The 23-item ‘Substance Use Risk Profile Scale’ (SURPS) [64] will be used to assess for variation in personality risk for substance abuse/dependence along four dimensions: sensation seeking, impulsivity, anxiety sensitivity and hopelessness.

#### ***Peer pressure***

The 10-item *‘*Resistive Self-Regulatory Efficacy Scale’ [65,66] will be used to measure participants’ perceived efficacy to resist peer pressure to engage in high risk activities.

#### ***Program evaluation and teacher log books***

Upon completion of the *CLIMATE Schools* programs, students and teachers will be asked to evaluate the program. Students will be asked to indicate how acceptable, appropriate and enjoyable they found the program and to indicate how likely it is they will use the information in their own lives. Teachers will be asked to rate the program; a) overall, b) in comparison to other substance use education programs, and c) in relation to the educational quality of the program. Teachers will also be asked to indicate how easy the program was to implement, how well it held students’ attention, and how likely it is that they would use the program in the future.

#### ***Implementation and treatment fidelity***

All teachers delivering the *CLIMATE Schools* programs will be asked to complete a logbook, indicating which lessons and activities they completed with their class and to write down any adaptations they made to the program. To ensure completion and fidelity of the online part of the program, students are required to view the lessons in full and in order. Students are not able to access the next lesson until they have completed the previous online lesson in full.

#### ***Record of additional substance use and mental health education***

Health and Physical Education teachers across all of the four study groups will be asked to record any substance use and/or mental health education that was delivered to students and/or their parents that was in addition to the *CLIMATE Schools* programs. Specifically teachers will be asked about the length, content and delivery method of this education.

#### ***Statistical analysis***

Single-level analyses; one-way analyses of variance (for normally distributed data), Chi-square (for binominal data), and Mann-Whitney U-test (for non-normally distributed data) will be used to examine baseline equivalence and attrition between groups. Due to the multi-level and hierarchical nature of the data, mixed effects regression will be used to examine intervention by time interaction effects. To account for intracluster variance within States or schools, intervention effects will primarily be examined using hierarchical linear modelling (HLM) for normally distributed data and hierarchical generalized linear modelling using a Poisson distribution for count data. Outcome variables will be centred at post-test to allow for comparisons between groups immediately after the intervention, and growth terms will be analysed to determine the magnitude of the follow-up effects. Analyses will be conducted using the program Stata. If unconditional models reveal that less than 10% of systematic variance exists at the between State or between school level for any outcome variable, HLM will be abandoned and single-level analyses will be used [67]. For these variables, ANCOVAs utilising the SPSS GLM procedure will be conducted to account for any baseline differences that might exist between groups. For multiple comparisons Bonferroni adjustments will be made. Effect sizes, odds ratios and 95% confidence intervals will also be calculated.

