### Study design

To establish the effectiveness of the integrated CSC intervention, a cluster RCT will be conducted in 84 Australian secondary schools between 2014 and 2016. Cluster randomisation will be employed to avoid contamination of the control group with the intervention group through student communication. Participating schools will be randomly allocated to one of four groups; (1) the *CLIMATE Schools - Combined* condition (CSC), (2) the *CLIMATE Schools* - *Substance Use* condition (CS-SU), (3) the *CLIMATE Schools - Mental Health* condition (CS-MH), or (4) the Control condition (CO). See Table 1 for a graphical display of the experimental design.

**Table 1 T1:** Experimental design

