### Sample size calculations

To account for cluster randomisation, sample size calculations were based on recent sample size requirements developed by Heo & Leon [49]. to detect intervention by time interactions in longitudinal cluster randomised clinical trials. The CSC trial will be powered to detect differences in the overall sample as well as between samples from each of four groups within the three States of NSW, QLD and WA. To allow for comparisons within each State, six schools (with at least 100 students) in each of the four intervention groups are required per state, giving a total of 24 schools per State (at least 2400 students). This achieves 80 per cent power to detect a standardized between-group mean difference of 0.15 (p = 0.05) in outcomes at the end of the trial with seven measurement occasions. An effect size of 0.15 is comparable to previous school-based trials of universal mental health and substance use prevention programs and would have substantial benefits on a population level based on recent economic modelling [50]. To account for school dropouts during the trial, which we expect to be approximately 10 per cent, we aim to recruit at least 28 schools in each State (at least 2800 students). This will result in an overall sample of 8400 students from 84 schools at baseline to test the efficacy of the CSC intervention in comparison to the other groups. Based on previous research using the *CLIMATE Schools* programs, school participation rates for similar trials were approximately 30 per cent [48,51]. Therefore, to recruit a total of 84 schools, approximately 270 schools will be approached to participate.

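### Baseline equivalence and attrition are tested with single-level methods although schools are randomised, so the false-positive rate is well above 5%

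*Protocol article*

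**What the plan says.** In the Protocol article, the Statistical analysis section opens with "Single-level analyses; one-way analyses of variance (for normally distributed data), Chi-square (for binominal data), and Mann-Whitney U-test (for non-normally distributed data"), and says that these "will be used to examine baseline equivalence and attrition between groups". The next sentence turns to the intervention effects and takes a different approach: "Due to the multi-level and hierarchical nature of the data, mixed effects regression will be used to examine intervention by time interaction effects".

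The Study design section states that "a cluster RCT will be conducted in 84 Australian secondary schools between 2014 and 2016" and that "Participating schools will be randomly allocated to one of four groups". Under Sample size calculations, "six schools (with at least 100 students) in each of the four intervention groups are required per state". The recruitment target is then raised: "To account for school dropouts during the trial, which we expect to be approximately 10 per cent", the aim becomes at least 28 schools per State, and "This will result in an overall sample of 8400 students from 84 schools at baseline".

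The Measures section says that gender, age, country of birth, academic performance and truancy are collected to establish baseline equivalence, so several variables will go through these tests.

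**The concern.** The school is the unit of allocation. Students in one school resemble each other, so an arm mean varies more between replications than a single-level test assumes. The test then rejects too often even when randomisation has worked. The section recognises the hierarchical structure one sentence later, but applies it only to the intervention effects.

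The problem is sharper for attrition. The sample-size section expects whole schools to leave. If their students count as lost, a student-level chi-square takes one school's withdrawal as about 100 independent losses.

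These are the only methods the article names for judging whether the arms were comparable at baseline and whether loss differed by arm. At stake is whether readers are told of imbalance or differential loss that is no more than chance variation between schools.

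A smaller point is that the Mann-Whitney test, named for non-normal data, compares two groups, while the design has four.

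**Working it through.** **Inputs from the article.** Four arms; 84 schools; at least 100 students per school; 8400 students; about 10% school dropout. Equal allocation gives 84/4 = 21 schools and 21 × 100 = 2100 students per arm.

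**The plan's own figure.** 6 schools × 4 arms = 24 per State. Allowing for 10% dropout, 24/0.9 = 26.7, so 27; 28 gives 7 per arm. Then 28 × 3 = 84 schools and 84 × 100 = 8400 students. The target reproduces, and the dropout allowance is clearly for whole schools.

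**Assumed.** The ICC, shown as a range because the article gives none. The significance level is taken as 5%.

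**Baseline variables.** With m students per school, the variance of an arm mean is inflated by the design effect DE = 1 + (m − 1) × ICC. The single-level four-arm test has 3 degrees of freedom and a critical value of 7.815, so its true size is P(χ²₃ > 7.815/DE). With m = 100:

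| ICC (assumed) | DE | 7.815/DE | True size | Simulated ANOVA |
|---|---|---|---|---|
| 0 | 1.00 | 7.81 | 5.0% | 4.9% |
| 0.005 | 1.50 | 5.23 | 15.6% | 15.3% |
| 0.01 | 1.99 | 3.93 | 26.9% | 26.8% |
| 0.02 | 2.98 | 2.62 | 45.4% | 45.0% |
| 0.05 | 5.95 | 1.31 | 72.6% | 72.5% |

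The simulation used 4000 trials per row, each with 4 arms × 21 schools × 100 students and no true difference. In the same trials, an ANOVA on school means had a size of 4.8% to 5.1% over these ICCs, so taking the school as the unit restores the nominal level.

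**Attrition by loss of whole schools.** Ten per cent of 84 is about 8 schools. Suppose 8 leave at random with respect to arm, all their students count as lost, and no others are lost.

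- The mildest uneven split is 3/2/2/1, that is 300, 200, 200 and 100 students lost of 2100 per arm. The expected loss is 200 per arm, so χ² = (100² + 100²)/200 + (100² + 100²)/1900 = 100 + 10.5 = 110.5, far beyond 7.815.
- The same split counted in schools (3, 2, 2 and 1 of 21) gives χ² = 1.1, p about 0.78.
- Hence only an exact 2/2/2/2 split escapes rejection. Its probability is C(21,2)⁴ / C(84,8) = 210⁴ / 43,595,145,594 = 0.0446.
- The student-level test therefore rejects in 1 − 0.0446 = 95.5% of trials in which arm has no effect on loss.

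**Variants, simulated.** If each school leaves with probability 10%, and 20% of students in retained schools are also lost (assumed), the rejection rate is 96% to 97% for ICCs of 0 to 0.10. With the 20% student loss and no school dropout, it is 27%, 46% and 73% at ICCs of 0.01, 0.02 and 0.05.

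**Mann-Whitney.** Four arms make six pairs. Six unadjusted pairwise tests have a familywise error of about 20% even with independent students. Testing each at 0.05/6 brings this back to about 5%, but does nothing about clustering.

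**The case against.** The best defence is that these are descriptive checks. Intervention effects are examined primarily with mixed and hierarchical models, and no sentence makes those models depend on a baseline or attrition test. This stands: the checks do not bias the primary mixed-model estimates.

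A reader might infer that a spurious imbalance would steer baseline adjustment. The text does not support that. ANCOVA is triggered when less than 10% of the variance lies between States or schools, and it then adjusts for any baseline differences whatever the tests showed.

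A reader might also infer that the tests will nearly always reject. For baseline variables this goes too far: at ICCs of 0.005 to 0.02 the test still fails to reject more often than not, and the article gives no ICC. For attrition the near-certain rejection is conditional. It needs the students of a withdrawn school to be counted as lost, which the article does not say. Nor does the article say that all attrition is at school level; it only allows for school dropout in the sample size. Without school dropout, the error rate again depends on the ICC.

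On the Mann-Whitney test, ANOVA and chi-square handle four arms, and the section promises Bonferroni adjustment for multiple comparisons, which may cover pairwise use. So this is a secondary matter of wording. It is not a separate reason to expect false imbalance.

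What the defence does not answer is that the article names single-level tests outright. This is not a detail left open for an analysis plan.

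**Conclusion.** The concern holds. In a trial that randomises schools, the stated tests have a false-positive rate well above 5%. For each baseline variable it is about 16% to 73% over assumed ICCs of 0.005 to 0.05, with 100 students per school. For attrition it is about 95% when roughly the expected number of schools leave at random and their students count as lost; that figure needs no ICC. The consequence is a misleading account of comparability and differential loss. It is not bias in the primary mixed-model estimates. The change should be made, but the trial's main conclusions do not turn on it.

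**What to change.** - Compare arms at baseline with methods that respect schools, either models with a school random effect or an analysis of school-level summaries.
- Report attrition in two parts: the number of schools lost by arm, analysed with the school as the unit; and the loss of students within retained schools, by mixed-effects logistic regression on arm with a school random effect.
- State whether students of a withdrawn school count as lost in any overall attrition figure.
- For non-normal variables, replace the Mann-Whitney test with a four-group method that respects schools.

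The cost is a few sentences of wording and routine work in Stata, which the trial already uses. Design, sample size and data collection are unaffected.

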### Procedure

#### Recruitment of schools and randomisation

The recruitment, inclusion, and randomisation of the participants (schools and students) will commence in September 2013. A total of 270 schools will be selected from a list of all public, independent and catholic schools in NSW, QLD and WA. The Principals of these schools will be sent a letter outlining the aims of the research, school requirements, time-frames, details of the randomisation procedure and an invitation for their school to participate. School Principals will then be followed up with a further email and phone call to invite their school to participate and explain the study requirements. Following school consent, randomisation will occur using the *Ralloc* function in Stata, and schools will be allocated to one of the four intervention groups shown in Figure 1.

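### The hierarchical models treat State as a variance level and use its estimated share in the 10% rule, although there are only three States and each is a named target of comparison

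*Protocol article*

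**What the plan says.** The Statistical analysis section sets the main model: "To account for intracluster variance within States or schools, intervention effects will primarily be examined using hierarchical linear modelling". It goes on: "If unconditional models reveal that less than 10% of systematic variance exists at the between State or between school level for any outcome variable", HLM is to be dropped for that outcome in favour of single-level analyses, run as ANCOVAs. No fixed State effect is mentioned.

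Under Sample size calculations, the trial is to detect differences overall and "between samples from each of four groups within the three States of NSW, QLD and WA". For this, "six schools (with at least 100 students) in each of the four intervention groups are required per state", which makes 24 schools per State. Allowing for school dropout, "which we expect to be approximately 10 per cent, we aim to recruit at least 28 schools in each State", or 84 schools in all. Strengths and limitations repeats that all four conditions can be compared both nationally and within each State.

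Recruitment of schools and randomisation describes allocation with the Ralloc function in Stata and says "schools will be allocated to one of the four intervention groups", referring to Figure 1. The text names no stratum. Figure 1 is not available in the copy reviewed.

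**The concern.** The phrase about variance within States or schools is loose, but the rule that follows is not. A between-State share taken from an unconditional model is an estimated variance component. Two things speak against using one here.

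First, three States leave 2 degrees of freedom for that component, too few for a useful estimate. Yet the estimate is an input to the choice between a multilevel and a single-level analysis, outcome by outcome.

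Second, a random State effect treats the States as draws from a wider population. The plan treats them as three specific places, each with its own comparison of arms. Fixed State effects with arm-by-State terms answer that question directly.

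What is at stake is mainly the decision rule. The rule joins State and school with *or*. Read literally, a low State share alone would be enough to abandon HLM, and school clustering would go with it even where the school share exceeds 10%. School is the unit of randomisation.

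**Working it through.** **Inputs from the article.** 3 States; 28 schools per State; 84 schools; at least 100 students per school; 4 arms; at least 6 schools per arm per State; 10% threshold.

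**Assumptions.** The article gives no variance shares, so they are varied below. Total variance is set to 1, schools have 100 students each, the outcome is normal, and one occasion is considered.

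**The plan's own counts.** 6 × 4 = 24 schools per State. 24 / 0.90 = 26.7, so 27, and the next multiple of four is 28. 28 × 3 = 84. These reproduce.

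**How precise is a State share from three units?** Let S, C and E be the State, school and student variances.

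- Variance of a school mean within a State: v = C + E/100.
- State mean square: (28S + v) × χ²(2)/2.
- School mean square: v × χ²(81)/81, where 81 = 84 − 3.
- Estimated State variance: (State mean square − school mean square)/28, set to zero if negative.
- Estimated share: that estimate divided by (itself + school mean square + 0.99E).

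With S = 0.10, C = 0.10 and E = 0.80, v = 0.10 + 0.80/100 = 0.108, and the expected State mean square is 28 × 0.10 + 0.108 = 2.908. Ignoring the small error in the school mean square, the share falls below 10% when the State mean square is below 2.908, its own expectation. χ²(2)/2 is exponential with mean 1, so the probability is 1 − e⁻¹ = 0.632. With C = 0.12 and E = 0.78, v = 0.1278 and the result is the same. Simulation of the full expression gives:

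| True State share | Assumed school ICC | Chance that the estimated State share is below 10% |
|---|---|---|
| 0 | 0.05 | 100% |
| 0.02 | 0.05 | 99.3% |
| 0.05 | 0.05 | 87% |
| 0.05 | 0.10 | 87% |
| 0.10 | 0.10 | 63% |
| 0.10 | 0.12 | 63% |

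The 63% needs care. Even a precise estimator would fall below the threshold about half the time when the truth lies on it. The spread is more telling: with S = 0.10 and C = 0.10, the 5th to 95th percentiles of the estimated share are about 0.2% and 25%. A true share of 5% is estimated above 10% in about 13% of trials (100 − 87). If the true share is zero (school ICC 0.05), the estimate is exactly zero with probability P(F(2, 81) < 1) = 0.63.

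The first rows bear on the literal *or*. If the true State share is small, the State condition is met almost always, whatever the school share is.

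**Does fixed versus random State matter for the national contrast?** A simulation on school means (84 schools, school ICC 0.05, State variance 0 to 0.10, 1,500 runs each) compared State as fixed with State as a REML random intercept. With 7 schools per cell the arm estimates are identical. Without State strata they differ on average by 0.002 to 0.007 SD, against a standard error of about 0.076. Type I error is 4.0–5.1% (fixed) and 3.9–5.5% (random). This covers intercepts only, not State-by-time slopes.

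**Allocation, conditional on no State stratum.** Randomly permuting 84 schools with 21 per arm and 28 per State, all 12 cells have at least six schools in about 5% of allocations (4.7–4.8%). Under simple randomisation the figure is about 0.5%. At least one cell has four or fewer in about 66% of the balanced allocations. Taking the stated 80% at 6 v 6 as given, within-State power is Φ(√(k/(1/a + 1/b)) − 1.96), with k = (1.96 + 0.8416)² × (1/6 + 1/6) = 2.616. For 4 v 7 this is Φ(√(2.616/0.3929) − 1.96) = Φ(0.62) = 73%. For 3 v 7 it is 65%. With State strata and balanced blocks, 28/4 = 7 per cell is certain at allocation.

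**The case against.** The best case for the plan has four parts.

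- **The random-effects structure is not spelled out,** and an analysis plan may give it. The within-State comparisons could also be run separately in each State, where no State component arises. This stands as far as the outcome model goes. It does not touch the 10% rule, which the article itself states and which needs a between-State share.
- **No harm to the arm effect is shown.** This largely stands for the national comparison. A reader might infer that a random State effect biases that comparison or inflates its error rate; the simulation above does not support this.
- **Three units do not give the interval one might quote.** The 95% factors of 0.27 and 39.5 from χ² on 2 degrees of freedom apply to the raw variance of three State means, which includes school sampling noise. They are not an interval for the State component, which can reach zero. This is right, so the argument rests on the estimated shares instead.
- **Missing stratification is silence in a condensed article.** This also stands. Figure 1 is not shown, and 28 schools per State, which is 7 × 4, suggests allocation by State. A reader might infer that allocation was unstratified and that the six-per-cell requirement is broken. The article supports neither.

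The different school year in Queensland adds little, because the same 13–14 age band is recruited in every State.

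**Conclusion.** The concern holds for State as a variance level and as an input to the 10% rule. The estimated State share is too imprecise to choose an analysis: at a true share of 10%, it falls below the threshold in about 63% of trials and ranges from almost nothing to a quarter of the variance. These figures rest on assumed school ICCs of 0.10 to 0.12, with 28 schools of 100 students per State.

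The loss of school clustering follows only if the *or* in the rule is meant literally. The wording allows that reading but does not settle it. The school side of the rule is a separate weakness, which making State fixed does not by itself repair.

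On allocation there is only a point to confirm. The 5% figure describes what would happen without a State stratum; it is not shown to be the trial's design.

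**What to change.** 1. Enter State as a fixed effect, with arm-by-State terms (and their time terms where the effect is an arm-by-time interaction) for the within-State comparisons.
2. Take the between-State share out of the 10% rule.
3. Keep the school and student random effects in every outcome model, whatever the estimated shares.
4. State whether allocation was stratified by State. If it was, say so and give the intended seven schools per arm per State. If it was not, report the actual cell counts and the within-State power that they give.

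The cost is wording, 2 degrees of freedom for State, and 3 × 2 = 6 for the arm-by-State terms. With 84 schools and 12 cells, 84 − 12 = 72 school-level degrees of freedom remain. No extra data are needed, and the national arm contrast is expected to change little.

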#### ***Alcohol and other substance use***

Students will be asked to rate the frequency and quantity of their alcohol consumption in standard drinks, frequency of drinking to excess (defined as having more than five standard drinks on a single occasion), age of first alcohol consumption for both a sip, full drink and drinking to excess, the maximum number of standard drinks they have consumed on one occasion, the proportion of their friends who drink and their intention to try alcohol. These questions were originally adapted from the School Health and Alcohol Harm Reduction Project (SHAHRP) ‘Patterns of Alcohol’ index [52] and trials of the ‘*Preventure’* program [53], and reflect those used in previous *CLIMATE Schools* trials [47,48,51,54]. Other drug use will be measured by questions based on the 2010 National Drug Strategy Household Survey (NDSHS) [45] and the 2011 Australian Secondary Students Alcohol and Drug Survey (ASSAD) [55]. This allows for comparison between use in the current sample and a large scale representative group of Australians. Students will also be asked to rate on a five-point Likert scale, ranging from ‘*very likely’* to ‘*very unlikely’,* how likely it is that they will try alcohol, cannabis and any other drugs in the future.

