#### ***Other substance use measures***

Alcohol related harms will be assessed using the 23-item Rutgers Alcohol Problem Index (RAPI) [56]. Students will be asked to rate how many times in the past six months they have experienced harms such as, “*neglected my responsibilities”,* as a consequence of drinking alcohol, on a five point Likert scale ranging from ‘*never’* to ‘*more than 6 times’*. Alcohol related knowledge will be assessed using a 16-item questionnaire originally adapted from the SHAHRP ‘Knowledge of Alcohol’ index [52], and reflect those used in previous trials using the *CLIMATE Schools* programs [47,48,51,54]. Participants’ knowledge about cannabis will be assessed by the 16-item ‘Knowledge about Cannabis’ scale used in previous *CLIMATE Schools* trials [47,48,51,54].

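### The hierarchical Poisson model for counts carries no allowance for residual overdispersion, so intervention-by-time tests on substance use could be anti-conservative

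*Protocol article*

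**What the plan says.** The Statistical analysis section of the protocol article states that "mixed effects regression will be used to examine intervention by time interaction effects". Count outcomes are assigned to "hierarchical generalized linear modelling using a Poisson distribution for count data". The purpose given for the hierarchy is "To account for intracluster variance within States or schools"; no student-level effect is named. The section mentions no dispersion check, alternative count distribution or robust variance.

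Two further statements limit how far the Poisson model reaches:

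- If less than 10% of the systematic variance of an outcome lies between States or between schools, "HLM will be abandoned and single-level analyses will be used", with ANCOVA as the replacement.
- The article does not list which outcomes are counts. Under Alcohol and other substance use, students "rate the frequency and quantity of their alcohol consumption in standard drinks, frequency of drinking to excess" and other items. Under Other substance use measures, the alcohol-harm items are rated "on a five point Likert scale ranging from" never to more than six times.

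**The concern.** A hierarchical Poisson model sets the variance equal to the mean only after conditioning on its random effects. School or student intercepts absorb differences that persist across surveys. The intervention-by-time test is judged against something else, namely how much counts move from survey to survey within students and how much school trends differ. If that movement exceeds Poisson variation, the model-based standard error of the interaction is too small.

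The design makes such movement plausible. Students are 13 to 14 at baseline and are surveyed seven times over 30 months. The questionnaire records age at first sip, first full drink and first drinking to excess, and delayed initiation is an expected effect. Students who move from zero to non-zero at different surveys create within-student variation that no intercept captures.

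Use of alcohol and cannabis is among the primary hypotheses. Understated standard errors would give intervals that are too narrow and could turn noise into a claimed effect. The planned Bonferroni adjustment does not help, because it assumes that each individual p-value is valid.

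**Working it through.** **The plan's own figure.** The only quantitative target is 6 schools per arm per State for 80% power at a standardized difference of 0.15 over seven occasions. A slope-difference formula, with 100 students per school, time variance 4 (occasions 0 to 6) and slope 0.15/6 = 0.025, gives

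schools per arm = 2(1 − ρ)(1.96 + 0.842)² / (100 × 7 × 4 × 0.025²).

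A within-student correlation ρ of 0.33 gives 6.01 schools (power 79.9% at 6), and ρ = 0.40 gives 5.38, rounded up to 6. The article does not state ρ, so the 6 is attainable but cannot be confirmed. It rests on a standardized mean difference and says nothing about count dispersion, so it neither supports nor weakens this point.

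**Closed form.** If the true variance of the interaction estimate is φ times the model-based variance, the test statistic has standard deviation √φ under no effect. The true size of a two-sided 5% test is then 2(1 − Φ(1.96/√φ)). The article gives no φ, so a range is assumed.

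| φ | 1.96/√φ | True size |
|---|---|---|
| 1 | 1.960 | 5.0% |
| 1.5 | 1.600 | 11.0% |
| 2 | 1.386 | 16.6% |
| 3 | 1.132 | 25.8% |

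**Simulation with no intervention effect.** Two arms were simulated, each with 21 schools of 100 students and seven surveys (84 schools divided equally over four arms), 1,000 runs per setting. The Poisson group-by-linear-time slope was fitted by conditional likelihood. With balanced data, the estimate and model standard error are the same whether one conditions on student, conditions on school or pools. The absence of a named student effect therefore does not drive the result. All variance settings are assumptions.

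| Source of extra variation | Variance/mean at survey 4 | Model SE / true SE | Size, Poisson SE | Size, school-clustered robust SE (t, 40 df) |
|---|---|---|---|---|
| None | 1.02 | 1.01 | 4.6% | 5.0% |
| Stable student effect, log-variance 1 | 2.48 | 1.00 | 5.4% | 5.8% |
| Stable student effect, log-variance 2 | 5.62 | 1.02 | 4.9% | 5.0% |
| Student effect (1) + survey-level gamma variance 0.5 | 3.52 | 0.65 | 20.2% | 6.1% |
| Student effect (1) + survey-level gamma variance 1 | 4.59 | 0.55 | 30.1% | 4.6% |
| Student effect (1) + survey-level gamma variance 2 | 6.57 | 0.41 | 41.2% | 4.9% |
| Student effect (1) + school slopes, SD 0.03, not modelled | 2.50 | 0.55 | 26.5% | 5.6% |

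The third row matters most for interpretation. A variance/mean ratio of 5.62 at a survey does no harm when it comes from stable differences between students. The damage comes from variation over time, within students or in school trends.

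**Staggered onset.** A separate null simulation added no gamma noise and let students start drinking at different surveys. It assumed 600 students per arm, 10% drinking at baseline, about 7% starting at each later survey (10% + 6 × 7% = 52% by the last, so just under half never start), a mean of 1 to 4 per survey once drinking, and a stable student SD of 0 to 1. The size of the nominal 5% test was 17% to 56%. With the same average trend but no staggered onset it was 5% to 6%. The wide range shows how strongly the result depends on the assumed onset pattern.

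**The case against.** Several points on the other side stand.

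- A reader might infer that the plan forces variance to equal the mean at each survey. It does not. That equality is conditional on the random effects, and the marginal variance may be much larger.
- A reader might infer that many zeros and a few heavy drinkers are enough to invalidate the test. The stable-student-effect rows show that they are not.
- A reader might infer that the standard errors are certain to be too small. The article reports no dispersion and no between-school variation in trend, so the harm is possible and plausible but not demonstrated.
- A reader might treat all drinking and harm measures as counts. The article does not label them. Drinking frequency may be recorded in categories, the harm items are five-point ratings, and harms are a secondary outcome. Uptake may be analysed as binary.
- The 10% rule may remove some count outcomes from the Poisson model altogether.
- This is a condensed article. It excludes neither robust errors nor a student-level effect, and an analysis plan that is not shown may specify either.

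The last point does not dispose of the matter. The distribution is not left open: Poisson is named without qualification for the intervention-by-time analysis, and a stated choice can be assessed as stated. The other points narrow the concern to count outcomes that stay hierarchical and make its size conditional.

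**Conclusion.** The concern holds in conditional form. The article fixes a hierarchical Poisson model for counts, names random variation only at State and school level, and states no allowance for residual overdispersion. For a substance-use outcome that is analysed as a count and retained in that model, extra variation from survey to survey within students, or unmodelled school-by-time variation, could make the interaction test anti-conservative. Under assumed residual variance ratios of 1.5 to 3, the true size is about 11% to 26% instead of 5%. If extra variation is confined to stable differences between students, it stays near 5%. The calculations assume balanced data, a linear time contrast and a two-sided 5% test; the article does not state sidedness. The documents do not support saying that the error will occur, or that it affects the harm scores or every drinking measure.

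**What to change.** Amend the sentence on count data so that the Poisson mean model is kept, but intervention-by-time tests and confidence intervals use standard errors robust to overdispersion and clustered by school. Add a small-sample correction for within-State comparisons, where two arms of 6 schools leave about 6 + 6 − 2 = 10 degrees of freedom. In the simulations this variance, with t reference on 40 df for 42 schools, held size between 4.6% and 6.1% in every setting tabulated.

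The alternative is a mixed-effects negative binomial model with student and school random effects, preferably also with school-clustered robust errors. Negative binomial alone may not be enough for staggered onset, because a student who starts drinking tends to stay above zero at later surveys, and that is not independent noise at each survey.

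The change is one sentence of analysis text. It costs slightly wider intervals if the counts prove to be Poisson, and occasionally slower convergence.
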